## Abstract

**Background:**

Stroke remains a leading cause of long-term disability globally, with upper limb impairment persisting in 39% of survivors at six months. The post-acute rehabilitation gap, characterized by precipitous decline in therapy intensity after hospital discharge, compromises recovery during critical neuroplastic windows. While robot-aided therapy (RAT) demonstrates efficacy comparable to conventional therapy, widespread implementation remains limited by cost, complexity, and facility-based care models. Home-based, minimally supervised RAT with telemonitoring could address these barriers while providing intensive therapy without proportional increases in healthcare resources.

**Objective:**

To evaluate the feasibility, acceptability, clinical effectiveness, and cost-effectiveness of home-based minimally supervised RAT using a portable planar robot in patients with moderate upper limb impairment following stroke.

**Methods:**

This pragmatic, single-arm, multi-center prospective trial will recruit 54 adults with subacute to chronic stroke (>28 days post-event) with upper extremity impairment (Fugl-Meyer Assessment 10–60) across three tertiary rehabilitation centers in Singapore. The intervention comprises four weeks of intensive home-based, caregiver-supervised training using the H-Man robot (60–120 min daily) with weekly telemonitoring, combined with four conventional occupational therapy sessions over an eight-week treatment period. The primary outcome is utilization rate (≥75% compliance) measured by cloud-based metrics. Secondary outcomes include motor impairment (FMA-UE), functional capacity (ARAT), quality of life (EQ-5D-5L), usability (System Usability Scale), and technology acceptance, assessed at baseline, 6, 8, 12, and 24 weeks. Economic evaluation will assess cost-effectiveness from healthcare system and societal perspectives.

**Results:**

Recruitment commenced October 2024 across three Singapore rehabilitation hospitals. The study employs rigorous safety monitoring, standardized training protocols, and cloud-based performance tracking. Preliminary feasibility testing demonstrates acceptable device usability and caregiver support requirements.

**Conclusion:**

TRUST addresses critical gaps in post-stroke rehabilitation by evaluating a scalable model combining technology-enabled home therapy with remote clinical oversight. Results will inform implementation strategies for integrating home-RAT into standard care pathways, potentially transforming stroke rehabilitation delivery in resource-constrained healthcare systems facing growing demand from aging populations.

**Clinical trial registration:**

ClinicalTrials.gov, identifier NCT06270459.

## Introduction

1

### The burden of stroke and upper limb dysfunction

1.1

Stroke represents a major global health challenge, ranking as the second leading cause of death with 6.2 m worldwide, accounting for 11% of all deaths; and the third leading cause of disability-adjusted life years lost worldwide (1). The societal impact extends far beyond acute mortality, with survivors experiencing persistent functional impairments that profoundly affect independence, quality of life, and caregiver burden. Upper extremity (UE) motor impairment emerges as one of the most prevalent and disabling sequelae, persisting in approximately 39% of stroke survivors at six months post-event (2). This persistent dysfunction significantly limits activities of daily living, vocational participation, and social engagement, creating cascading effects on psychological wellbeing and family dynamics.

In Singapore, stroke is the 4th leading cause of death, accounting for 5.6% of all deaths and affecting 9.3% of adults over 65 years (3). The burden of stroke is projected to increase substantially by 2030 as a consequence of rapid population aging in Singapore and its official status in 2026 as a superaged society (3). The age-adjusted prevalence of ischemic stroke reaches 125.06 per 100,000 person-years, with hemorrhagic stroke at 44.19 per 100,000 person-years (4). Stroke rehabilitation is a lifeline of hope for stroke survivors and caregivers from early days to years’ post-stroke as it reduces stroke-related complications, dependency, disability, institutionalization and increase functional independence and societal reintegration. These demographics underscore the urgent need for scalable, effective rehabilitation interventions that can meet growing demand while maintaining quality within resource constraints.

### The post-acute rehabilitation gap

1.2

Critical and chronic discontinuity characterizes the local stroke rehabilitation continuum, manifesting as a precipitous decline in therapy intensity following hospital discharge. During inpatient rehabilitation, patients typically receive intensive daily therapy (3h, 3H/day) aligned with evidence-based recommendations for optimizing neuroplastic recovery. However, this intensity drops dramatically post-discharge, with first outpatient contact varying from 2–6 weeks and subsequent therapy frequency ranging from biweekly to monthly sessions (5). This “rehabilitation cliff effect” causes a major systemic mismatch for the critical neuroplastic window when recovery potential remains high but vulnerability to deterioration peaks.

The consequences of inadequate post-acute rehabilitation extend beyond delayed recovery. Learned non-use, characterized by progressive abandonment of the use of the affected limb despite residual function, develops through repeated failure experiences and compensatory strategies (6). Hidaka et al. (7) demonstrated through computational modeling that the bidirectional relationship between arm function and use creates feedback loops—increased use promotes functional improvement, while decreased use accelerates decline. These dynamics underscore the critical importance of maintaining therapy intensity during the post-acute phase.

### Robot-aided therapy: evidence and implementation barriers

1.3

Robot-aided therapy has emerged as an evidence-based approach to deliver high-intensity, task-specific rehabilitation addressing fundamental challenges in stroke care. The mechanistic basis for RAT effectiveness lies in enabling high-dose repetitive practice that promotes use-dependent plasticity while providing precise kinematic and kinetic measurement for objective progress monitoring (8). Multiple systematic reviews and meta-analyses demonstrate that RAT achieves outcomes comparable to dose-matched conventional therapy for motor impairment reduction, with potential advantages when used as an adjunct rather than replacement (9, 10).

Despite robust evidence, RAT implementation remains severely limited. Commercial systems cost SGD 100,000–500,000, require dedicated space and technical support, and lack reimbursement coverage in many healthcare systems. These barriers confine RAT primarily to well-resourced rehabilitation centers, perpetuating access inequities. The COVID-19 pandemic further exposed vulnerabilities in facility-based models, with service disruptions disproportionately affecting stroke survivors requiring consistent intensive therapy (11).

This manuscript describes a pragmatic trial protocol rather than a systematic review; accordingly, no formal systematic search strategy was employed. The background evidence summarized in the Introduction is drawn from landmark systematic reviews, meta-analyses, and seminal trials in robot-aided stroke rehabilitation identified through targeted literature review of key databases (PubMed, Cochrane Library) and citation tracking of foundational works in the field. A comprehensive list of supporting references is provided.

### The H-Man system: democratizing access to robotic rehabilitation

1.4

The H-Man robot, developed through collaboration between Nanyang Technological University and Tan Tock Seng Hospital, represents a paradigm shift in rehabilitation robotics design philosophy. Prioritizing accessibility over complexity, H-Man achieved CE Mark certification as a Class 2A medical device in 2020 for hospital, clinic, and critically, home use. At approximately 25% the cost of commercial alternatives, weighing 14 kg, and requiring only 880 × 700 mm table space, H-Man addresses key implementation barriers (12).

Technical specifications reflect careful balance between functionality and simplicity. The planar manipulandum with two active degrees of freedom enables reaching and drawing movements fundamental to upper limb function. The H-shape cabled differential transmission provides intrinsic safety through mechanical compliance, eliminating complex force-limiting software that increases cost and reduces reliability. A previous randomized controlled trial demonstrated that H-Man-assisted therapy combined with conventional therapy achieved motor improvements statistically equivalent to duration-matched conventional therapy alone in 44 chronic stroke survivors, with no serious adverse events and high satisfaction scores (13, 15).

### Study rationale and objectives

1.5

Current care models in Singapore’s public healthcare institutions cannot provide daily intensive rehabilitation without substantially increasing resource burden. The shift from facility-centric to home-based care using affordable, portable robotic technology could ensure therapy continuity while addressing multiple access barriers. This pragmatic trial evaluates real-world implementation of home-RAT across diverse healthcare settings, prioritizing generalizability and inclusivity over experimental control.

The primary objective is to determine the utilization rate of home-based RAT, defined as the proportion of prescribed sessions completed (≥75% threshold), as this directly informs implementation viability. Secondary objectives include: (1) establishing feasibility and acceptability of home-RAT implementation across multiple sites; (2) evaluating clinical effectiveness on motor and functional outcomes; (3) assessing economic viability from healthcare system and societal perspectives; and (4) identifying implementation facilitators and barriers to inform scale-up strategies.

## Methods

2

### Study design and setting

2.1

This pragmatic, single-arm, multi-site prospective trial employs an implementation-effective hybrid design (Type 2) prioritizing both clinical outcomes and implementation factors (14). The single-arm design was selected over randomized controlled trial designs based on the presence of: (1) extensive existing evidence for RAT equivalent efficacy in comparison with usual care; (2) ethical considerations about withholding potentially beneficial intervention with a randomized control design employing a control group; (3) practical challenges of standardizing rehabilitation treatment control conditions across sites; and (4) the pressing need to evaluate the feasibility, QOL and cost-effectiveness of delivering home-RAT rather than efficacy under ideal or standardised or highly supervised home-training conditions.

The study is conducted across three major public healthcare institutions in Singapore:Tan Tock Seng Hospital (TTSH), National Healthcare Group Health (NHG health): Lead site with Singapore’s first and largest rehabilitation medicine department with extensive rehabilitation technology clinical practice and research experience.Singapore General Hospital (SGH), Singapore Health Services (Singhealth): Nation’s largest hospital with integrated acute-subacute-outpatient rehabilitation servicesNational University Hospital (NUH), National University Health System (NUHS): Academic medical center with Integrated academic health system with strong translational research infrastructure

Each site serves demographically and clinically distinct populations. TTSH predominantly manages older adults with higher neurological complexity through its specialized rehabilitation centre, SGH serves a broad acute-to-chronic case mix through its integrated rehabilitation pathway, and NUH draws from its academic health system catchment with a higher proportion of younger stroke survivors and research-naïve participants. These sites employ different care models, enhancing generalizability while testing implementation robustness across contexts.

### Participants

2.2

#### Eligibility criteria

2.2.1

Several eligibility criteria warrant clarification regarding operationalization. ‘Near-normal function’ is defined as FMA-UE > 60, indicating minimal residual motor impairment insufficient to benefit meaningfully from robotic-assisted training. ‘Medical stability’ is determined by the referring rehabilitation physician based on the absence of acute intercurrent illness, haemodynamic instability, or uncontrolled comorbidities requiring active medical titration within the preceding two weeks. ‘mild cognitive impairment’ is operationalized as a Montreal Cognitive Assessment (MoCA) score ≤21, consistent with the cognitive inclusion threshold. All eligibility determinations are documented by the site principal investigator using a standardized screening checklist. Participants with mild shoulder subluxation (≤1 finger-breadth) or controlled pain (VAS ≤ 5/10) and, pain is monitored longitudinally using the Visual Analogue Scale at all assessment timepoints (see Table 1).

**Table 1 tab1:** Inclusion and exclusion criteria.

Domain	Inclusion criteria	Exclusion criteria
Diagnosis	Confirmed ischemic or hemorrhagic stroke Neuroimaging confirmation by neurologists or neurosurgeons	Non-stroke etiology of impairment Stroke impairment mimics
Demographics	Age 21–90 years Both genders	Pregnancy or lactation
Timing	>28 days post-stroke	Life expectancy <6 months
Motor Function	MRC ≥ 2/5 shoulder/elbow FMA 10–60	Complete paralysis Near-normal function
Cognitive	MOCA >21/30 Ability to consent/assent and understand demands of study	Mild cognitive impairment Active psychiatric illness
Physical	Sitting tolerance >60 min Medical stability	Orthostatic hypotension Active seizures Medical instability Severe shoulder subluxation (≥2 finger-breadths) with pain at rest Uncontrolled upper limb pain (VAS > 5/10 at rest) unresponsive to analgesia
Environmental	Stable home during trial duration Available caregiver	Homeless or unstable housing Absence of reliable caregiver /No support system/Resident of nursing home
Medical	Controlled comorbidities	Uncontrolled medical illness Active cancer

#### Sample size calculation

2.2.2

Sample size determination used non-inferiority framework with utilization rate as primary outcome. Based on 70% utilization in clinic-based programs (historical controls) and 5% non-inferiority margin, 18 participants per site (*n* = 54 total) provides 80% power at *α* = 0.10 (one-sided). This sample accounts for an anticipated 15% dropout rate (approximately 8 participants), yielding a minimum evaluable sample of 46 participants. Dropout is defined as withdrawal of consent, loss to follow-up, or inability to complete ≥50% of the home-RAT phase. Sensitivity analyses will compare intention-to-treat (all enrolled) and per-protocol (≥75% session completion) populations.

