### Statistical analysis plan

2.7

The primary analysis evaluates non-inferiority of the observed utilization rate against a 70% historical benchmark derived from clinic-based RAT programs, with a pre-specified non-inferiority margin of 5%. Non-inferiority is demonstrated if the lower bound of the one-sided 95% confidence interval for the observed utilization rate exceeds 65%. This analysis follows intention-to-treat principles, including all enrolled participants regardless of completion status; participants who withdraw are assigned zero utilization for remaining sessions.

For secondary clinical outcomes (FMA-UE, ARAT, grip strength, EQ-5D-5L, SIS-16, PROMIS-10), linear mixed-effects models are employed with fixed effects for time (categorical: baseline, Week 6, Week 8, Week 12, Week 24), site, and baseline severity (FMA-UE score), and a random intercept for participant to account for within-subject correlation across repeated measures. An unstructured covariance matrix is specified, with model fit compared against compound symmetry using the Akaike Information Criterion. The assumption of normally distributed residuals will be assessed using Q-Q plots and the Shapiro–Wilk test; non-normal outcomes will be analysed using generalized linear mixed models with appropriate link functions. Multiple comparisons across secondary outcomes are controlled using the Benjamini-Hochberg False Discovery Rate procedure at q = 0.05.

Exploratory subgroup analyses examine treatment effect heterogeneity by stroke chronicity (<6 months vs. ≥6 months), baseline severity (FMA-UE < 30 vs. ≥30), age (<65 vs. ≥65 years), and cognitive status (MoCA 21–25 vs. >25) using interaction terms in the mixed models. These are hypothesis-generating and interpreted cautiously given the sample size.

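### The 80% power stated for 54 participants cannot be reproduced from the stated rate, margin and alpha, and it does not describe the primary analysis in section 2.7

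*Protocol article*

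**What the plan says.** All references are to the protocol article.

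- **Design (2.1).** "This pragmatic, single-arm, multi-site prospective trial employs" a hybrid design. There is no concurrent control, so the primary comparison is a one-sample test.
- **Sample size (2.2.2).** "Sample size determination used non-inferiority framework with utilization rate as primary outcome". The inputs are given as "Based on 70% utilization in clinic-based programs (historical controls) and 5% non-inferiority margin", and the result as "18 participants per site (*n* = 54 total) provides 80% power at *α* = 0.10 (one-sided". The section then allows for "an anticipated 15% dropout rate (approximately 8 participants), yielding a minimum evaluable sample of 46 participants". It names no SD and no expected home rate.
- **Primary outcome (2.5.1.1).** Utilization is worded as a percentage of sessions, where a day counts once it has at least 30 minutes of active exergaming. A success threshold of 75% is attached. The abstract and section 1.5 also pair the rate with 75%.
- **Primary analysis (2.7).** "Non-inferiority is demonstrated if the lower bound of the one-sided 95% confidence interval for the observed utilization rate exceeds 65" per cent. All enrolled participants are included, and "participants who withdraw are assigned zero utilization for remaining sessions".

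**The concern.** Section 2.2.2 presents a definite power together with the figures it is said to rest on, and those figures do not lead to it. Three features of section 2.7 then move the analysis away from the one that was sized: a stricter alpha, a larger analysis set, and zeros after withdrawal.

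The primary conclusion is a yes/no statement on non-inferiority. If the real power is well below 80%, a missed bound is a likely result even when home use matches the clinic benchmark. A reader who trusts the 80% would take that miss as evidence against home therapy.

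**Working it through.** **Inputs.** Null rate 70% − 5 = 65% (2.2.2, 2.7). True rate 70%, meaning equality with the benchmark; this is the usual convention and the only rate in 2.2.2. One-sided alpha 0.10 (2.2.2) or 0.05 (2.7). n = 54, or 46 after dropout (54 × 0.85 = 45.9, so that step is consistent). Normal quantiles: 1.2816 (alpha 0.10), 1.6449 (alpha 0.05), 0.8416 (80% power).

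**1. Attempt to reproduce 80%: proportion of participants, alpha 0.10, n = 54.**

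- Normal, variance at 70%: SE = √(0.21/54) = 0.0624; power = Φ(0.05/0.0624 − 1.2816) = Φ(−0.48) = 31.6%.
- Normal, null variance for the critical value: √(0.2275/54) = 0.0649; power = Φ((0.05 − 1.2816 × 0.0649)/0.0624) = Φ(−0.53) = 29.7%.
- Exact binomial: at least 41 of 54 are needed (size 0.059); power 21.4%.
- n = 46: 29.4%, 27.6% and 23.3% (at least 35 of 46).

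Required n for 80%:

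- null variance for the critical value: ((1.2816√0.2275 + 0.8416√0.21)/0.05)² = 398;
- variance at 70% throughout: 379.

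This is about 7 times the plan (379/54 = 7.0).

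Other combinations do not repair it. A true rate of 75% gives 51–66% at alpha 0.10. Superiority, 75% against 70%, gives 25–33%. Of the variants tried on this scale, only 65% against 75% at one-sided alpha 0.20 with no dropout gives 54 participants and 80% (80.4%), and 2.2.2 states neither that alpha nor that true rate.

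**2. Mean of per-participant percentages.** The largest SD that still gives 80% power is SD = δ√n/(z for alpha + 0.8416), where δ is the distance of the true rate from 65%. For example, 5 × √54/2.123 = 17.3.

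| True rate | n | alpha 0.10 | alpha 0.05 |
|---|---|---|---|
| 70% (δ = 5) | 54 | 17.3 | 14.8 |
| 70% | 46 | 16.0 | 13.6 |
| 75% (δ = 10, assumption) | 54 | 34.6 | 29.6 |
| 75% (assumption) | 46 | 31.9 | 27.3 |

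Power at n = 54 and a true 70%, for assumed SDs:

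| SD (assumed) | alpha 0.10 | alpha 0.05 |
|---|---|---|
| 15 | 88% | 79% |
| 20 | 71% | 58% |
| 25 | 57% | 43% |
| 30 | 48% | 34% |

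**3. Effect of the rule in 2.7 on the proportion scale.** At alpha 0.05 and n = 54, power at 70% is 13.5% exact and 18–20% by normal approximation. A Wald or Wilson bound gives 21%.

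**4. Effect of dropout under 2.7.** Assume that 15% drop out within the training weeks with average utilization m, and hold the overall mean at 70%. Completers then average (70 − 0.15m)/0.85. The split between the two groups alone contributes an SD of √(0.15 × 0.85) × (completer mean − m).

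- m = 25: completers 77.9, SD 18.9, so power at n = 54 is at most 75% (alpha 0.10) or 62% (alpha 0.05), even if there is no other spread.
- m = 0: completers 82.4, SD 29.4, so at most 49% or 35%.
- m = 49 with a within-completer SD of 10: overall SD 12.8, so 94–95% or 89%.

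If instead completers average exactly 70%, the all-enrolled mean is 0.85 × 70 + 0.15m. That is 59.5 at m = 0 and 67.0 at m = 50.

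**The case against.** The best defence is that the outcome is not binary. Section 2.5.1.1 words it as a percentage of sessions, and zeros for remaining sessions only make sense on that scale. The results in the first step of the working would then not apply. A planned home rate above the benchmark is also possible. At an assumed 75%, the success threshold, 80% power is reached with an SD of about 32–35 points at alpha 0.10, or about 27–30 at alpha 0.05. These inputs may stand in the full protocol or an analysis plan, and an article need not print them.

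This stands as far as it goes. A reader might infer that the true power is 21–32% and that a comparable home programme would most likely fail. The documents do not support that without conditions, because those figures hold only if each participant counts as a success or failure. On the mean scale, an assumed SD of 25 gives 57% power at alpha 0.10 and 43% at alpha 0.05.

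The dropout figures are conditional too. Home training ends at week 4 and follow-up runs to week 24, so someone lost at week 12 counts as a dropout but has complete utilization data. The statement "yielding a minimum evaluable sample of 46 participants" is a customary allowance and can be right for analyses that exclude dropouts; beside an all-enrolled analysis it is not a contradiction in itself.

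The defence does not restore the printed statement. The article attributes 80% to a 70% rate, a 5-point margin and alpha 0.10, and these alone do not yield it. The difference between alpha 0.10 and the one-sided 95% bound remains on either scale.

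**Conclusion.** The concern holds in this form: the stated 80% cannot be reproduced from the stated inputs, and it refers to a different alpha from that of the primary analysis.

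- If utilization is a proportion of participants and the true rate is 70%, power at alpha 0.10 is about 21–32% (n = 54) or 23–29% (n = 46). Under the section 2.7 rule it is about 13–20% at n = 54.
- If it is a mean percentage, power is undetermined until an SD and a true rate are named. At 70% and n = 54, 80% needs an SD of at most about 17 points at alpha 0.10, or about 15 under section 2.7.
- For the primary analysis, dropout during the training weeks lowers the mean and widens the spread; it does not reduce n to 46. How much depends on when dropouts leave, which is an assumption.

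Confidence is high on non-reproducibility and on the mismatch in alpha. The documents do not settle what the power actually is, so they do not justify calling the test low-powered outright or recomputing the historical 70%.

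**What to change.** In section 2.2.2:

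1. Replace the 80% statement with the power, or the expected width of the confidence bound, for the section 2.7 analysis: all 54 enrolled, zeros for remaining sessions after withdrawal, one-sided alpha 0.05. Name the scale, the SD and the assumed true rate, with training-phase dropout already in the last two. As an example of bound width, an assumed SD of 25 puts the lower bound 1.645 × 25/√54 = 5.6 points below the mean. On the proportion scale at 70% it is 1.645 × √(0.21/54) = 10.3 points below.
2. Make alpha agree between sections 2.2.2 and 2.7.
3. Limit the 46-evaluable figure to analyses that exclude dropouts.
4. If the restated power is well below 80%, present the estimate and its bound as the main result, and say that a missed non-inferiority bound is not to be read as failure of home therapy.

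The cost is one rewritten paragraph and one aligned alpha, with no extra patients. The downside is that the stated power will probably be less favourable.

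### The 80% power is quoted at one-sided alpha 0.10, but the only stated decision rule is a one-sided 95% bound (alpha 0.05), so the power belongs to a looser test than the one planned.

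*Protocol article*

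**What the plan says.** Two sections of the protocol article fix the error level for the primary outcome, the utilization rate.

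- Section 2.2.2 (Sample size calculation) starts from "70% utilization in clinic-based programs (historical controls) and 5% non-inferiority margin". It says that "18 participants per site (*n* = 54 total") "provides 80% power at *α* = 0.10 (one-sided"). It adds: "This sample accounts for an anticipated 15% dropout rate (approximately 8 participants"), "yielding a minimum evaluable sample of 46 participants".
- Section 2.7 (Statistical analysis plan) tests "non-inferiority of the observed utilization rate against a 70% historical benchmark derived from clinic-based RAT programs", "with a pre-specified non-inferiority margin of 5"%. The criterion follows: "Non-inferiority is demonstrated if the lower bound of the one-sided 95% confidence interval for the observed utilization rate exceeds 65"%. All enrolled participants are analysed, and those who withdraw count as zero for their remaining sessions.

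The benchmark (70%), the margin (5 points) and hence the limit (65%) agree. The error level does not.

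**The concern.** A lower confidence bound and a one-sided test are the same procedure. A one-sided 95% lower limit above 65% rejects the null value of 65% at one-sided alpha 0.05. The bound that matches one-sided alpha 0.10 is a one-sided 90% limit, which is easier to clear. Section 2.2.2 therefore reports the power of one test and section 2.7 runs a stricter one.

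The trial has a single arm and a fixed benchmark, so this bound is the whole primary decision. A reader who takes the 80% at face value will overrate the chance that the trial can meet its own criterion. A failure to show non-inferiority would then be read as stronger evidence against home-based delivery than it is.

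**Working it through.** **Inputs from the article.** Null limit 70% − 5% = 65%; n = 54 enrolled, 46 evaluable; one-sided alpha 0.10 with 80% power (2.2.2); one-sided alpha 0.05 (2.7). The assumed true rate and the SD are not stated. Normal quantiles: z(0.90) = 1.2816, z(0.95) = 1.6449, z(0.80) = 0.8416.

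**Step 1. Can the stated 80% at one-sided 0.10 be reproduced?** Not from the stated inputs alone.

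- Per-participant percentage, true mean 70%: 80% power requires SD = 5 × √n / (1.2816 + 0.8416). This gives 16.0 points for n = 46 and 17.3 points for n = 54. Neither SD is in the article.
- Binary endpoint, true rate 70%, n = 54: power = Φ(0.05 × √54 / √(0.70 × 0.30) − 1.2816) = Φ(0.802 − 1.2816) = 31.6%. To reach 80%, the true rate would have to be about 78% (n = 54) or 79% (n = 46).

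The 80% therefore rests on an input that the article does not give. The next step takes it as correct.

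**Step 2. Effect of the alpha mismatch alone.** A design with 80% power at one-sided 0.10 has a standardized effect of 1.2816 + 0.8416 = 2.1232. At one-sided 0.05 its power is Φ(2.1232 − 1.6449) = Φ(0.478) = 68.4%. With the binary normal approximation that uses separate null and alternative variances, the figure is about 66%.

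Keeping 80% at 0.05 multiplies the sample by ((1.6449 + 0.8416)/(1.2816 + 0.8416))² = 1.37. On that basis 46 evaluable becomes 64, and 64/0.85 rounds up to 76 enrolled.

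**Step 3. Absolute power under each level (n = 54, true value 70%).**

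| Reading of the endpoint | One-sided 0.10 (2.2.2) | One-sided 0.05 (2.7) |
|---|---|---|
| Percentage, assumed SD 15 points | 88% | 79% |
| Percentage, assumed SD 20 points | 71% | 58% |
| Percentage, assumed SD 25 points | 57% | 43% |
| Percentage, assumed SD 30 points | 48% | 34% |
| Binary, normal approximation | 31.6% | 20.0% |
| Binary, exact | 21.4% (41 or more of 54) | 13.5% (42 or more of 54) |

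The percentage rows use Φ(5 × √54 / SD − z). For SD 20 this is Φ(1.837 − 1.2816) = 71% and Φ(1.837 − 1.6449) = 58%.

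**Step 4. What the two levels demand of the data.** For a percentage with an assumed SD of 20 points, the observed mean must exceed 65 + 1.2816 × 20/√54 = 68.5% at 0.10 and 65 + 1.6449 × 20/√54 = 69.5% at 0.05.

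**The case against.** Four arguments can be made on the other side.

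1. *There is only one decision rule.* A reader might infer that the error rate of the primary claim is open at 5% or 10%, and that the level could be picked after the result is known. The article does not support that. Only 2.7 says when non-inferiority is shown, and it uses the stricter level. Section 2.2.2 gives a planning assumption and no criterion. This argument stands: what is wrong is the quoted power, not the planned type I error.

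2. *The very low binary figures are not the plan's own inputs.* A reader might take 32% falling to 20% as the trial's actual power. Those figures assume a yes/no outcome per participant and a true rate of 70%. Section 2.5.1.1 defines a percentage of prescribed sessions, and the zero-utilization rule in 2.7 fits an average of such percentages, although the 75% threshold leaves some ambiguity. This also stands, and so the range is shown rather than one figure.

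3. *Opposite verdicts on one dataset depend on the interval method.* With 41/54, the exact (Clopper-Pearson) lower limit is 66.9% at the 90% level and 64.5% at the 95% level, which looks like a pass turned into a fail. But at the 95% level the Wilson limit is 65.3% and the Wald limit 66.4%, and both pass. Under those two methods the reversal falls at 40/54 instead. The article names no method, so no single count shows the reversal for this plan. That the levels set different hurdles remains true.

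4. *It may be a slip of one word.* A two-sided 90% interval has the same lower limit as a one-sided 95% bound. If 2.2.2 meant two-sided 0.10, the sections agree and no power is lost. This is possible, but 2.2.2 says one-sided and nothing in the article shows otherwise. As written it still needs correcting.

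**Conclusion.** The inconsistency is real and explicit: both levels are printed for the same primary test, so leaving detail to a fuller document cannot explain it. The power in 2.2.2 does not describe the rule in 2.7.

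The part that the mismatch itself causes is a drop from 80% to about 68%, conditional on the 80% at one-sided 0.10 being correct under some unstated true rate or SD. The absolute power cannot be settled from the article. It lies anywhere from 79% down to 34% for a percentage endpoint with the assumed SDs of 15 to 30 points, and lower still for a binary endpoint with a true rate of 70%. Every reading examined shows a loss in moving from 0.10 to 0.05. The failure to reproduce 80% even at 0.10 is a separate matter, but it means that changing the alpha label alone would not make the 80% valid.

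**What to change.** - Keep the one-sided 95% lower bound in 2.7 as the decision rule.
- In 2.2.2, replace one-sided alpha 0.10 by one-sided alpha 0.05. If two-sided 0.10 was meant, correct the word 'one-sided' instead.
- Restate the power of the 54 enrolled (46 evaluable) at that level, and give the assumed true utilization rate and SD beside it.

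The change needs no new data and leaves the analysis rule as it is. The rewording is short, but the power has to be recalculated from stated assumptions. The cost is that the stated power will probably look less favourable, unless 'one-sided' was only a labelling slip.
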